### **Background and Introduction**

With advancements in diagnostic techniques, cancer treatments and adjunctive therapies, the overall survival rate of pediatric brain tumors have been remarkably increased. However, numerous studies have indicated that the improved pediatric cancer survival has inevitably been accompanied by increased chronic physical problems and adverse psychological late-effects of cancer and its treatment. The frequently reported physical and psychological sequelae included cancer-related fatigue, reduced muscle strength, decreases in functional capacity, activity intolerance, depression and distorted self-esteem, which in turn severely comprises their quality of life (QoL). Among these sequelae, cancer-related fatigue is the most common problem experienced by pediatric cancer survivors. Substantial evidence has revealed that adaptation in regular physical activity can reduce cancer-related fatigue, enhance muscle strength and improve functional capacity. Nevertheless, considerable concern has been raised towards the declining levels of physical activity among pediatric cancer survivors. In a local cross-sectional study which assessed the physical activity and the factors affecting regular exercise among 128 young Hong Kong Chinese cancer survivors revealed that their current physical activity levels were markedly reduced when compared with the pre-morbid situation. The study also showed that cancer-related fatigue is the most significant factor that prevented the survivors from engaging in regular physical activity. Alarming, evidence shows that physical inactivity can lead to a wide array of health problems, including muscle catabolism and atrophy and

cardiovascular diseases, which in turn may further exaggerate cancer-related fatigue and lead to a reduction in pediatric cancer survivors' functional capacity, hence causing long-term decrement in their QoL. In light of the breadth and long lasting nature of those aforementioned negative impacts of cancer, healthcare professionals should therefore take a proactive role in offering prompt support and developing appropriate interventions that can help reduce fatigue among young cancer survivors, and increase their awareness of the importance of regular physical activity.

A large body of evidence supports that regular physical activity has beneficial effects on both physical and psychological well-being of pediatric cancer survivors. In addition, evidence shows that engaging in regular moderate-intensity physical activity may help ameliorate some of the treatment-related adverse effects experienced by pediatric cancer survivors. Such benefits include reduced cancer-related fatigue and improved physical fitness, functional capacity, muscle strength, immunity, and bone health, all of which contribute to an overall reduced risk of morbidity and an enhancement in QoL. Given the long-term health benefits associated with regular, moderate levels of physical activity, there is an imperative need to advocate the idea of having regular physical activity in pediatric cancer survivors. To this end, the development and evaluation of appropriate strategies that can increase the adoption and maintaining of regular physical activity among pediatric cancer survivors is crucial.

There are several reasons to dissect why Hong Kong Chinese pediatric cancer survivors reported substantially low physical activity levels. First, due to the influence of the philosophy of Confucianism, which focuses on the maintenance of harmony in our bodies to attain health, survivors' parents or healthcare professionals may held the misconception that physical activity. As children exhibited fatigue after their recovery from cancer, which may have led parents to

be hesitant to encourage their children to perform energy-consuming activities such as physical activity. Thus, pediatric cancer survivors are often advised to take more rest to avoid cancer- or treatment-related fatigue. Further, many pediatric cancer survivors show reluctance to perform PA, and Chinese parents may be gentler and more tolerant to this attitude after their child's recovery. Nevertheless, physical inactivity can accelerate fatigue as it induces muscle catabolism and atrophy, which in turn may lead to a further decrease in functional capacity. Second, owing to the relatively low body resistance of pediatric cancer survivors, they are often discouraged by their parents to go to crowded public areas, and hence this may hinder their engagement in physical activity. Third, in the society of Hong Kong, rooted in the Confucian traditions, most of the Chinese parents perceive achievement in academic and other domains, such as music and art, as important indicators for determining their child's capability and future possibilities. In addition, due to the extremely competitive environment for education in Hong Kong, parents always strive for opportunities to gain educational advantages for their child to maximize their child's probability of enrolling in an elite school. Therefore, Hong Kong Chinese pediatric cancer survivors are required to make extra efforts to catch up with their studies after the suspension from school during the treatment. Consequently, there will be less time available for pediatric cancer survivors to engage in regular physical activity. Further, most Chinese pediatric cancer survivors reported that there is lack of encouragement by their important ones and role models to follow and learn the appropriate physical activities for them to engage in. Indeed, parents are influential in affecting the activities that the children performed, and parental psychological control may inhibit the development of positive mental well-being and affect emotional life in Chinese children. Therefore, it is crucial to understand the perception of engagement of regular physical activity of the pediatric cancer survivors from their parents'

perspectives, with the aim at developing appropriate intervention for the pediatric cancer survivors to adopt and maintain regular physical activity.

The decline in physical activity levels among Hong Kong Chinese pediatric cancer survivors may be largely due to the overlook of the significance of regular physical activity by survivors' parents and their misconception about performing physical activity during their child's survivorship, which all resulted in exhibiting ambivalence and low motivation to encourage their children engaging in regular physical activity. Thus, it is imperative for the healthcare professionals to instill proper concept to the parents regarding the adoption and maintenance of regular physical activity, with the aim of enhancing Hong Kong Chinese pediatric cancer survivors' physical well-being and improving their QoL.

A substantial body of evidence has demonstrated that education alone is insufficient or unlikely to change behavior. MI is a directive, client-centered counseling strategy which differs from prevailing patient education to support clients to explore and resolve their ambivalence about changing their behaviors. MI has demonstrated efficacy and effectiveness in promoting positive health behavioral changes, for instance, oral health, alcohol and other substance use. Yet, traditional MI requires an intensive treatment, which may not be feasible to be implemented in the Hong Kong context due to the busy life. A brief MI that emphasises the adoption of shorter and simpler style of counselling was thus developed. MI involves elicitation of individual's motivation, enhancement of individual's commitment, and exploration of solutions toward change of behavior through four stages, namely engaging, focusing, evoking and planning. Engaging involves the process of establishing a collaborative relationship with the client by expressing empathy through reflective listening. Focusing is the ongoing process of guiding the client to identify a specific area about which the client is ambivalent to make a

change. Evoking focuses the elicitation of the client's intrinsic motivation for change by developing discrepancy between the client's goals or values and his or her current behavior. Planning involves making and consolidation of a commitment to change as well as developing an action plan to adapt to a new behavior.

### **Rationales of using mobile instant messaging applications as a mean to deliver brief motivational interviewing**

There is an increase in the use of information communication technology (ICT) for health care delivery and health promotion. According to the definition by the World Health Organization, mobile health refers to medical and public health practice which are supported by mobile devices using instant messaging (IM) applications, such as WhatsApp or WeChat. ICT are expanding rapidly worldwide, it is a new strategy to promote health. Using IM applications (i.e. WhatsApp or WeChat) allows quick, direct and continuing professional advice and support for the parents to manage their child's level of physical activity. Instant messaging can be delivered instantaneously that can be accessed at a time that suits recipients. In addition, instant messaging is more cost-effective than face-to-face meetings and offers for mutual communication, in which parents can elicit feedback and interact flexibly.

### **Research Plan and Methodology**

#### ***Study design***

An assessor-blinded prospective RCT will be conducted in two pediatric outpatient clinics in two public hospitals in different districts of Hong Kong. The aim of the RCT is to examine the effects of a brief MI delivered to parents via mobile instant messaging on PA levels, cancer-related fatigue, handgrip strength (HGS), peak expiratory flow rates (PEFR), and QoL among Chinese pediatric cancer survivors. Participants will be recruited from the two pediatric

oncology outpatient clinics in Hong Kong. The parent-child dyads who meet the criteria will undergo baseline assessments before randomization. The method of simple complete randomization will be adopted. Subjects will be randomly allocated to experimental or control groups. Randomization will be performed by a research assistant opening a sequentially numbered, opaque sealed envelope with a card inside indicating the allocated group. The random numbers to be used for group assignment will be computer-generated by another research assistant before subjects recruitment begins. Allocation concealment will thus be ensured.

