### ***Subjects***

#### **a) Pediatric cancer survivors**

Hong Kong pediatric cancer survivors meeting the inclusion criteria will be invited to participate in this study. The inclusion criteria included (1) children aged from 9 to 16 years, (2) able to communicate in Cantonese and read Chinese, (3) have completed treatment for at least six months previously, (4) does not participate in physical exercise in the previous 6 months. Survivors with evidence of recurrence or secondary malignancies and those with physical impairment, cognitive impairment, or impaired mental status identified from their medical records will be excluded.

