### ***Sample size calculation***

We used power analysis to estimate the sample size, referring to the results of our previous pilot study of the intervention and findings of our previous intervention studies on efforts to promote PA among pediatric cancer survivors in Hong Kong. An average moderate effect size (Cohen's  $d = 0.5$ ) was found for the outcomes of PA and fatigue levels, muscle strength, and QoL. Consultation with an expert panel, comprising a pediatric oncologist, a nursing specialist in pediatric oncology, and a professor and assistant professor from a local university, indicated that this result can be regarded as the minimally important difference that warrants a change in patient management. To detect a statistically meaningful between-group difference with a moderate effect size (Cohen's  $d = 0.5$ ) and a power of 80% (two-tailed; with a potential attrition rate of 20%) at  $\alpha = .05$ , a minimum of 160 parent–child dyads with 80 dyads per arm will be required.

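### Simple randomisation at two hospitals leaves arm sizes, hospital mix and age mix to chance, and the analysis model adjusts for neither hospital nor age

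*Combined protocol and SAP*

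**What the plan says.** The trial recruits from "two pediatric outpatient clinics in two public hospitals in different districts of Hong Kong" (Study design). On allocation, the same section says: "The method of simple complete randomization will be adopted". The list is prepared in advance: "The random numbers to be used for group assignment will be computer-generated by another research assistant before subjects recruitment begins". A research assistant then allocates each dyad by "opening a sequentially numbered, opaque sealed envelope with a card inside indicating the allocated group". No blocking, stratification or minimisation is described anywhere.

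The Sample size calculation section asks for at least 160 dyads, "with 80 dyads per arm will be required". Eligibility covers "children aged from 9 to 16 years" (Subjects, part a).

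Under Data analysis, the two groups are compared with t-tests and chi-squared tests, but no action is stated if they differ. The GEE model contains group, time and their interaction. Hospital and age are not mentioned as covariates.

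**The concern.** The size statement is written in terms of equal arms, and the allocation method does not produce equal arms except by luck. The same holds for the two obvious baseline factors, hospital and age. An imbalance would not be prevented by the design, and no planned adjustment would deal with it. The investigators could then be left choosing covariates after seeing the baseline table, which weakens the credibility of the result.

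Age is the factor of most interest. Handgrip strength and peak expiratory flow are recorded as raw physical measurements in children who are up to seven years apart in age (16 − 9) and are followed for 12 months. Variation due to age that is left unexplained adds noise to the treatment comparison.

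**Working it through.** **Inputs.** From Sample size calculation: d = 0.5, two-sided alpha 0.05, power 80%, attrition 20%, 160 dyads. From Study design: two hospitals, simple randomisation. Hospital shares and the age distribution are not given, so they are assumed and varied below.

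**1. The plan's own figure.** The two-sample t-test needs 63.8, so 64 completers per arm. 64 / (1 − 0.20) = 80 per arm, 160 in total. The stated size reproduces exactly.

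**2. Arm sizes.** If recruitment stops at 160, one arm's size is X ~ Binomial(160, 0.5), with SD = √(160 × 0.25) = 6.3.

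- P(X = 80) = 6.3%, so one arm is below 80 with probability 93.7%.
- P(85:75 or worse) = 2 × P(X ≤ 75) = 47.7%.
- P(90:70 or worse) = 2 × P(X ≤ 70) = 13.3%.
- 95% range for one arm: 68 to 92.

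**3. What unequal arms cost.** Power comes from the noncentral t distribution with n1 + n2 − 2 degrees of freedom and noncentrality 0.5 × √(n1·n2 / (n1 + n2)), with 80% retained in each arm.

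| Randomised | Completers | Noncentrality | Power |
|---|---|---|---|
| 80:80 | 64 / 64 | 0.5 × √32 = 2.83 | 80.1% |
| 70:90 | 56 / 72 | 0.5 × √31.5 = 2.81 | 79.5% |
| 68:92 | 54.4 / 73.6 | 0.5 × √31.28 = 2.80 | 79.3% |

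Averaged over all possible splits, power is 79.9%.

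**4. Balance on hospital or age.** This is the simulated chance that the arms differ by at least the stated amount in the share of dyads from one hospital (400,000 replicates, 160 dyads, assumed shares):

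| Hospital shares (assumed) | ≥ 10 points | ≥ 15 points |
|---|---|---|
| 50:50 | 24% | 6.6% |
| 60:40 | 21% | 5.7% |
| 70:30 | 18% | 4.1% |
| 80:20 | 12% | 1.9% |

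The 50:50 row also applies to a split at the median age. A normal approximation with both arms fixed at 80 gives SE = √(0.25/80 + 0.25/80) = 0.079 and P(≥ 10 points) = 20.6%. Within any one stratum of 80 dyads (assumed), 45:35 or worse has probability 2 × P(Binomial(80, 0.5) ≤ 35) = 31%.

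**5. With restriction.** Blocks of 4 can leave each stratum at most 2 dyads out of balance. With two hospital strata the worst difference is 2 × 2 = 4 (78:82, power 80.1%). With four strata it is 4 × 2 = 8 (76:84, power 80.0%). If the block size can be 6, the four-stratum limit is 4 × 3 = 12 (74:86, power 79.9%). N is unchanged throughout.

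**6. What adjustment could add.** Suppose hospital and age explain a share R² of an outcome's variance at a single time point. The effective standardised difference is then 0.5 / √(1 − R²). With 64 completers per arm, power becomes 80.9% at R² = 0.02, 82.1% at 0.05, 84.1% at 0.10 and 88.1% at 0.20. The documents give no R² for any outcome, so this is a range and not an estimate.

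**The case against.** The case for leaving the method alone is substantial, and most of it stands.

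- **Arm size.** The figure of 80 per arm is a planning target. A reader might infer from the 6.3% that the trial will be underpowered. Step 3 shows otherwise: the loss is under one percentage point even at the edge of the 95% range.
- **Validity.** A reader might infer bias. Simple randomisation with concealed envelopes is unbiased, and it is the least predictable scheme available.
- **Primary outcome.** A reader might infer that the 12-month activity result is at risk. Nothing in the documents links hospital or age to the activity score.
- **Hospital.** One nurse delivers all the brief motivational interviewing, mostly by smartphone, and follow-up assessments are home visits. Hospital may therefore matter little.
- **Existing model.** If baseline is one of the modelled time points, the group-by-time term compares changes from baseline, and stable age differences between the arms largely cancel. It does not remove differences in growth between younger and older children over 12 months.
- **Fatigue scale.** The scale is described for ages 7 to 12 while eligibility runs to 16. A reader might infer that stratifying by age would cure this. It would not, because it adds no child to the scale's stated age range. That mismatch is a separate issue.
- **Cost.** Stratifying is not free. The nurse who delivers the intervention knows the allocations, so small blocks in small strata can be partly guessed.

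What remains is narrower. The plan neither balances hospital and age by design nor adjusts for them in the analysis, although both are known for every dyad. If the list was in fact made with exactly 80 cards per arm, which the text does not say, the totals would balance but hospital and age would still be left to chance.

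**Conclusion.** The point holds as a modest improvement in efficiency and credibility; it is not a flaw that threatens validity. Power lost to unequal arms is negligible: about 0.2 points on average (80.1% to 79.9%) and 0.6 points at 70:90. A 10-point difference between arms in hospital mix has a chance of 12% to 24%, depending on the assumed hospital shares. The corresponding chance for an age split at the median is 24%, or about 21% by the normal approximation.

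The benefit of acting is in balance and precision. That it would be greatest for handgrip strength and peak flow is a plausible judgement about growing children, not a figure from the documents. No benefit for the primary activity score is demonstrated. The arm-size results assume that recruitment stops at 160 and that attrition is 20% in both arms.

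**What to change.** **If recruitment has not begun**, have the second research assistant regenerate the list in permuted blocks of randomly varying size (for example 4 and 6). Stratify by hospital and, if wanted, by two age bands (9-12 and 13-16). Prepare one envelope series per stratum, and keep the block sizes from everyone who recruits, allocates or treats. The cost is two or four envelope series in place of one and slightly more predictable allocation, which the concealed random block sizes limit. N stays at 160.

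**In either case**, prespecify hospital and age (continuous) as covariates in the GEE for every outcome, whatever the baseline tests show. State also how baseline values enter the model. If baseline is itself a modelled time point, let hospital and age interact with time, because a time-constant main effect hardly changes a comparison of change from baseline. If the baseline value is a covariate, main effects are enough. This needs only an amendment to the Data analysis section and has essentially no downside, so it is the part to do if only one is done.

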### ***Subjects***

#### **a) Pediatric cancer survivors**

Hong Kong pediatric cancer survivors meeting the inclusion criteria will be invited to participate in this study. The inclusion criteria included (1) children aged from 9 to 16 years, (2) able to communicate in Cantonese and read Chinese, (3) have completed treatment for at least six months previously, (4) does not participate in physical exercise in the previous 6 months. Survivors with evidence of recurrence or secondary malignancies and those with physical impairment, cognitive impairment, or impaired mental status identified from their medical records will be excluded.

#### **b) Parents of pediatric cancer survivors (either father or mother; the primary caregiver of pediatric cancer survivors)**

Parents of pediatric cancer survivors must be (1) able to speak Cantonese and read Chinese, (2) able to use a smartphone with an IM application (i.e., WhatsApp or WeChat) installed. Parents with emotional or psychiatric disorders, and cognitive and learning problems identified from their medical records will be excluded from the study.

### ***Sample size calculation***

We used power analysis to estimate the sample size, referring to the results of our previous pilot study of the intervention and findings of our previous intervention studies on efforts to promote PA among pediatric cancer survivors in Hong Kong. An average moderate effect size (Cohen's  $d = 0.5$ ) was found for the outcomes of PA and fatigue levels, muscle strength, and QoL. Consultation with an expert panel, comprising a pediatric oncologist, a nursing specialist in pediatric oncology, and a professor and assistant professor from a local university, indicated that this result can be regarded as the minimally important difference that warrants a change in patient management. To detect a statistically meaningful between-group difference with a moderate effect size (Cohen's  $d = 0.5$ ) and a power of 80% (two-tailed; with a potential attrition rate of 20%) at  $\alpha = .05$ , a minimum of 160 parent–child dyads with 80 dyads per arm will be required.

## ***Intervention***

### *(a) Intervention group*

As well as receiving scheduled medical follow-ups at the oncology outpatient clinic, children and parents will receive BMI and instant messaging delivered by a trained research nurse (RA).

#### In pediatric outpatient clinic

At the time of recruitment, both children and parents will receive a 10-minute health advice session on the significance of and misconceptions about regular physical activity for cancer survivors and strategies for overcoming barriers to engaging in physical activity delivered by a trained research nurse at the time of recruitment in the pediatric outpatient clinics. Parents will then receive a face-to-face brief MI session of approximately 10 minutes. In this session, parents will also be encouraged to motivate their children to intensify their physical activity levels progressively, with the ultimate goal at achieving the Global Recommendations on Physical

Activity on Health suggested by the World Health Organization. Additionally, they will be invited to visit a website from the Centre for Health Protection, Department of Health, HKSAR website (<https://www.chp.gov.hk/en/healthtopics/content/25/8804.html>) that contains information on physical activity. A comprehensive assessment will be conducted to children to identify appropriate types of physical activity for them by a research nurse who was trained by one of the coinvestigators, who is an assistant professor specializing in sports and recreation management. The assessment may involve assessing children's physical condition, for instance functional mobility, walking gait and balance. Children's preference on types of physical activity will also be discussed. All parents will be informed that they will receive an individual BMI intervention and instant messaging to facilitate the engagement in physical activity of their children via WhatsApp/WeChat on the smartphones throughout the study period.

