### ***Outcome measures***

The primary outcome measure is the level of physical activity of the survivors at 12 months after starting the intervention. The secondary outcome measures are survivors' levels of fatigue, left- and right-HGS, PEFR and QoL at baseline, 1, 3, 6, and 12 months after starting the intervention. Participants in both groups will be required to complete the questionnaires and assessments at baseline (during their medical follow-up), 1, 3, 6 and 12 months after starting the intervention (during home visits).

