#### ***Data collection***

To minimize attrition bias, intention-to-treat analysis will be used. Ethical approval will be obtained from the Institutional Review Board of the University of Hong Kong/Hospital Authority Hong Kong West Cluster and Hong Kong Children's Hospital Research Ethics Committee. Before commencement, the Chief of Service of the pediatric oncology unit will be briefed on the purpose, nature and protocol of this study. To identify potential subjects, the research assistant will approach pediatric cancer survivors who have their medical follow-ups in the pediatric outpatient clinic and ask them to indicate their willingness to participate in this study. After checking for eligibility, the research student will explain the study details, such as its nature, purpose, implications, and data collection procedure to each pediatric cancer survivors and their parents. If both the parent and the child agreed to participate, written consent will be obtained from the parents and the child's assent will be also obtained. The children and their

parents will be assured that their participation is completely voluntary and that all of the information provided will be kept confidential. The issue of confidentiality is the major ethical issue, and will be solved by recording the data in a manner that does not allow the participants to be identified (ie. using a non-recognizable code for each patient). This study will be conducted in compliance with the principle of Declaration of Helsinki and ICH-GCP.

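### The plan describes no recording or reporting of injuries or other adverse events in either arm, so no harm count by arm could be set beside the benefit

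*Combined protocol and SAP*

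**What the plan says.** Under the Subjects heading, the protocol selects children aged 9 to 16 with the criterion "does not participate in physical exercise in the previous 6 months". It excludes "Survivors with evidence of recurrence or secondary malignancies and those with physical impairment, cognitive impairment, or impaired mental status identified from their medical records". Under Intervention, in the outpatient clinic part, parents are "encouraged to motivate their children to intensify their physical activity levels progressively", with the WHO activity recommendations as the eventual goal. A nurse assesses each child in order to choose suitable activities: "The assessment may involve assessing children's physical condition, for instance functional mobility, walking gait and balance".

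Outcome measures states: "The primary outcome measure is the level of physical activity of the survivors at 12 months after starting the intervention". The secondary outcomes are fatigue, left and right handgrip strength, peak expiratory flow and quality of life. On timing: "Participants in both groups will be required to complete the questionnaires and assessments at baseline", and again by home visit at 1, 3, 6 and 12 months.

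The Data collection section commits the study to being run "in compliance with the principle of Declaration of Helsinki and ICH-GCP". Data analysis specifies generalized estimating equations for each outcome, with two-sided tests at .05. Neither section, nor Data Handling and Record Keeping, mentions injuries, adverse events, a reporting route or a safety analysis.

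**The concern.** The intervention aims to raise exertion in children who have been inactive. The Background itself describes survivors as prone to reduced muscle strength, lower functional capacity and poor tolerance of activity, and says that parents hesitate to encourage demanding activity. A count of injuries by arm is the information that would speak to that hesitation.

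The Sample size section calls the target effect the "minimally important difference that warrants a change in patient management". Anyone using a positive result to argue for such a change would want harms beside benefits. Under the plan as written there would be no event count in either arm, and falls or injuries that never reach a medical record could not be recovered afterwards.

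Ascertainment is a second point. Intervention parents usually have one to three messaging contacts a week for six months (about 26 to 78 contacts, taking 26 weeks), then lighter contact to month 12. Control parents receive no brief MI. If events were ever gathered from messages, they would come from one arm only.

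**Working it through.** **1. Where a harm item could sit.**
- Outcome measures and Measuring outcomes: physical activity, fatigue, handgrip, peak flow and quality of life only.
- Subjects: exclusions from medical records. This is screening before entry, not recording afterwards.
- Intervention, outpatient clinic: a nurse assessment described at recruitment, with optional physical content.
- Ensuring intervention integrity: message review and weekly meetings, directed at recruitment and quality of delivery.
- Data collection: the ICH-GCP sentence, with no definition, question or schedule.
- Data analysis: no safety analysis.

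None of these sets up recording of events in either arm.

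**2. The plan's own sample size.** Inputs from Sample size calculation: d = 0.5, two-sided α = .05, power 80%, attrition 20%. The normal approximation gives n = 2(1.960 + 0.842)²/0.5² = 62.8, so 63 per arm. The t-test gives 63.8, so 64 per arm. Then 64/(1 − 0.20) = 80 per arm, 160 in total. The plan's figure reproduces, and recording events does not alter it.

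**3. What recording would show within one arm.** With 0 events in n children, the one-sided 95% upper bound is 1 − 0.05^(1/n):
- n = 80: 3.7%
- n = 64 (after 20% attrition): 4.6%

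The two-sided 95% exact interval uses 1 − 0.025^(1/n), giving 4.5% and 5.6%.

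The chance of at least one event is 1 − (1 − p)^n. The documents give no event risk, so p is assumed:

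| Assumed risk p | n = 80 | n = 64 |
|---|---|---|
| 1% | 55% | 47% |
| 2% | 80% | 73% |
| 5% | 98% | 96% |

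**4. What recording would show between arms.** Power = Φ{[|p₁ − p₂| − 1.96·√(2p̄(1 − p̄)/n)] / √([p₁(1 − p₁) + p₂(1 − p₂)]/n)}, where p̄ is the mean of the two risks. For an assumed 5% versus 10% with n = 80: (0.05 − 1.96 × 0.04165)/0.04146 = −0.763, so power is 22%.

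| Assumed risks | n = 80 per arm | n = 64 per arm |
|---|---|---|
| 5% vs 10% | 22% | 19% |
| 10% vs 20% | 42% | 35% |
| 5% vs 15% | 56% | 47% |
| 5% vs 20% | 82% | 73% |

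Only a large excess would be detected reliably.

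**The case against.** The case on the other side has several parts.

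- *The intervention is mild and screened.* Parents are encouraged, progression is gradual, activity types are chosen after an assessment, and children with physical impairment or recurrence are excluded. This stands. A reader might infer that vulnerable children are being pushed into exertion without safeguards; the text does not support that.
- *The trial is not blind to deterioration.* Fatigue, handgrip, peak flow and quality of life (including eight physical-functioning items) are measured in both arms at five time points and tested two-sided. This stands. A reader might infer that the trial can say nothing about safety, but the gap is confined to discrete events.
- *Some events could be recovered.* Attendances and admissions are partly retrievable from medical records, which the team already uses for eligibility. This stands in part. It does not reach falls and injuries managed at home.
- *ICH-GCP implies safety duties.* It does, and consent material was not available to check. So the supportable statement is that no plan is described, not that no event will ever be noted. The sentence still supplies no question, schedule or analysis.
- *Nobody proposes to report harms from messages.* Correct. The one-sided ascertainment is a hazard to guard against, not something the plan commits.
- *The phrase about patient management only justifies d = 0.5.* Also correct. It is not a rule that practice will change on efficacy alone.
- *The counts would settle little.* The low power in the working bears this out, and children fall and attend clinics in any case, so attribution would be weak. That argues for descriptive reporting by arm, not for leaving the events unrecorded.

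**Conclusion.** The point holds in a limited form. The methods text describes no plan to record or report injuries or other adverse events in either arm. Followed as written, the trial could show worsening on its measured scales but could not give a harm count by arm, and home-managed falls and injuries would be lost.

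Recording them would allow a statement such as a risk below 3.7% (80 children) or 4.6% (64 children) if no events occurred, and would probably reveal an event type with a risk of 2% or more. It would not amount to a safety test. The detection and power figures rest on assumed event risks, and n = 64 rests on the plan's 20% attrition. This is an inexpensive improvement that should be made; it does not threaten the validity of the primary comparison.

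**What to change.** At the existing 1-, 3-, 6- and 12-month home visits, ask the same short fixed questions in both arms: activity-related injury or fall, unplanned medical attendance, and hospital admission since the last visit. Ask them after that visit's outcome assessments are finished, to protect the blinded assessor. Add to Data analysis a descriptive table of counts by arm with exact confidence intervals, stated not to be a powered comparison. Log events learned only through messaging separately, and leave them out of the between-arm comparison.

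No extra visit is needed, and the sample size stays at 160. The costs are a small data-entry burden, recall over up to six months (the interval from month 6 to month 12), and some remaining risk of unblinding, since a family may mention the coaching and the same assessor may return at a later visit.
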